### Sample size

Based on the phase 1 baseline census in 12 clusters, we estimate that we will achieve interviews with 350 married women aged 15 to 49 years per cluster, and that we will have information on 80 pregnancies in the preceding 2 years, 80 children born in the preceding 2 years, and 120 children over 2 and under 5 years of age. We estimate that we will manage to measure the weights and heights of 150 children under 5 years of age per cluster. The sample size calculations assume two treatment groups, unmatched clusters of approximately equal size, and values of *k* (coefficient of variation of true proportions between clusters) equal in intervention and control groups [18]. Table 1 summarizes expectations for the primary outcomes. Control area proportions and values of *k* are based on the phase 1 baseline census in 12 clusters. The estimates were all made at 80% power. Because the intervention is part of our service delivery program, is of minimal risk, and will be evaluated after 2 years of operations, we are not specifying stopping rules.

**Table 1 T1:** Detectable differences in primary outcomes between allocation groups, with 40 clusters allocated 1:1, intervention:control

**Indicator**	**Estimated records per cluster**	***k***	**Control estimate (%)**	**Intervention estimate (%)**	**Detectable difference (%)**	**Detectable relative difference (%)**
Unmet need for family planning	350	0.11	46	41	−5	11
Incomplete basic immunizations in children under 5 years of age	160	0.22	66	53	−13	17
Weight-for-height >−2SD below median for age and sex in children under 5 years of age	150	0.1	20	16	−4	20

Records per cluster, *k*, and control estimate based on phase 1 data for 12 clusters. *k*, coefficient of variation of true proportions between clusters; SD, standard deviation.

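### Table 1's 17% relative difference for immunization contradicts its own row (13/66 = 19.7%); a 17% reduction would have about 70% power, not 80%

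*Protocol article*

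**What the plan says.** The Sample size section of the protocol article plans for two arms with "unmatched clusters of approximately equal size, and values of" k equal in both arms, and Table 1 lists detectable differences "with 40 clusters allocated 1:1, intervention:control". The text adds: "The estimates were all made at 80% power". Alpha is not stated.

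The immunization row, "Incomplete basic immunizations in children under 5 years of age", gives 160 records per cluster, k = 0.22, control 66%, intervention 53%, difference −13 points, relative difference 17%.

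The wasting row reads "150 0.1 20 16 −4 20" in the same column order. The family-planning row has 350 records, k = 0.11, 46% against 41%, −5 points and 11%. Control rates and k come from the phase 1 baseline census in 12 clusters.

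**The concern.** The last column of Table 1 should be the absolute difference divided by the control rate. It is in the other two rows: 5/46 = 10.9%, printed as 11, and 4/20 = 20%, printed as 20. In the immunization row it is not.

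Incomplete immunization is one of three primary outcomes, and Table 1 is where the article states what the trial can detect for it. A reader who takes the relative column at face value concludes that 20 clusters per arm give 80% power for a 17% relative reduction. If that is wrong, the trial's sensitivity on this outcome is overstated.

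**Working it through.** **1. Division within the row (no assumptions).** 66 − 53 = 13, and 13/66 = 19.7%. Both rates are printed as whole percents, so allow each its rounding interval:
- smallest relative difference: (65.5 − 53.5)/65.5 = 18.3%
- largest: (66.5 − 52.5)/66.5 = 21.1%

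The printed 17% lies outside this range.

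**2. Formula.** The stated assumptions (unmatched clusters, a common k) match the usual coefficient-of-variation formula for clusters per arm:

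c = 1 + (z_α/2 + z_β)² × [p0(1−p0)/m + p1(1−p1)/m + k²(p0² + p1²)] / (p0 − p1)²

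with m the records per cluster. I assume two-sided 5%, so (1.96 + 0.84)² = 7.85. Turned round, power = Φ(√[(c − 1)(p0 − p1)²/V] − 1.96), where V is the bracketed term and c = 20.

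**3. Calibration on the family-planning row** (m = 350, k = 0.11, 46% v 41%):
- V = 0.000710 + 0.000691 + 0.004594 = 0.005995
- c = 1 + 7.85 × 0.005995/0.05² = 19.8
- power with 20 per arm = 80.4%
- solving for 80% power gives 41.0%, a difference of 4.98 points or 10.8%

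The row reproduces, which supports both the formula and the assumed alpha.

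**4. Immunization row** (m = 160, k = 0.22, control 66%):

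| Intervention rate | Difference (points) | Relative | Power, 20 per arm | Clusters per arm for 80% |
|---|---|---|---|---|
| 53% (as printed) | 13.0 | 19.7% | 83.2% | 18.5 |
| 53.5% (solved for 80%) | 12.5 | 19.0% | 80% | 20.0 |
| 54.8% (17% reduction) | 11.2 | 17.0% | 70.2% | 25.0 |

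For the last line, p1 = 0.66 × 0.83 = 0.5478, so V = 0.001402 + 0.001548 + 0.035607 = 0.038558 and √(19 × 0.1122²/0.038558) = 2.49. Power is Φ(2.49 − 1.96) = 70.2%.

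So 53% and −13 points follow from the inputs after rounding, and 17% does not. Rounding of k (0.215 to 0.225) and of the 17% itself (16.5% to 17.5%) moves the 70.2% between about 66% and 75%. Dropping the +1 from the formula gives 72.4%.

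**5. Could another alpha explain 17%?** One-sided 5% (equivalently two-sided 10%) gives a detectable immunization rate of 54.8%, which is 17.0% relative. The same row would then print 55% and −11 points, and the family-planning row would give 41.6%, printing as 42%. Neither agrees with the table.

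**6. Wasting row** (m = 150). With k = 0.10 and control 20% taken as exact, the detectable difference at 80% power is 3.3 points (20% to 16.7%), and the printed 4 points has 92.6% power. However:
- in whole points, 3 points (20% v 17%) has 71.2% power, so 4 is the smallest that reaches 80%;
- k is printed to one decimal, and a true k between about 0.121 and 0.149 gives a detectable rate of 16.5% to 16.2%, which prints as 16;
- at k = 0.10, a true control rate of 19.5% gives a detectable 16.2%, and any control rate up to about 19.8% still prints as 16.

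**The case against.** The strongest reply is that this is one derived cell. The control rate, intervention rate and absolute difference are sound, the printed contrast of 66% against 53% has 83% power, and the contradiction can be seen from the adjacent columns. The 70% figure belongs to a contrast (66% v 54.8%) that the table does not print as rates, and it rests on an alpha that the article does not state. All of this stands, and it limits the point to the relative figure. It does not rescue that figure: the 13/66 check needs no alpha, and the article presents the whole table as computed at 80% power.

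A reader might also infer that the wasting row is wrong, or that 17% and 20% were exchanged between the two rows. The documents do not support either. The wasting row is internally consistent (20, 16, −4, 20%), and rounding of its inputs or of its results can produce it. Any discrepancy there is conservative. Moving 17% into that row would break its agreement with its own 20, 16 and −4.

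Three smaller matters might be read as further errors:
- The text expects "80 children born in the preceding 2 years, and 120 children over 2 and under 5 years of age", 200 in all, while the row uses 160 records. Fewer usable records than listed children is not a contradiction, and using 200 changes 12.5 points only to 12.4.
- The row refers to basic immunizations, the primary outcome to full immunization for age. Nothing shows that the 66% came from a different definition.
- The wasting label puts a greater-than sign before −2SD, ahead of the words "below median for age and sex in children under 5 years of age". As a z-score this would describe children who are not wasted, but the outcome definition and the 20% control rate leave no doubt about what is meant. It is a notational slip.

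**Conclusion.** The point holds for one cell. The 17% relative difference for immunization contradicts its own row, where the printed rates give 19.7% (18.3% to 21.1% allowing for rounding). That much is arithmetic and rests on no assumption.

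The consequence for power assumes two-sided 5% and the unmatched-cluster formula, both supported by the family-planning row. On that basis the difference detectable at 80% power is 12.5 points (19% relative), and a 17% reduction has about 70% power and would need about 25 clusters per arm rather than 20. The error flatters the trial on a primary outcome, but it does not affect the number of clusters or the absolute planning difference. The wasting row is not established as an error.

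**What to change.** In Table 1, replace 17% in the immunization row with about 20% (19% if given from the unrounded 12.5 points), and keep 66%, 53% and −13 points. State the alpha beside the 80% power so that the table can be reproduced.

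Optionally, change the sign in the wasting label to <−2 SD, and print k and the wasting rates to more decimals, so that a reader can see whether 4 points is a rounded or an exact figure. A short note on why 160 rather than 200 immunization records are expected, and that the 66% uses the for-age definition, would remove two queries.

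The cost is a table correction. Clusters, outcomes and analysis stay as they are; the stated sensitivity for immunization becomes slightly less favourable.

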### Randomization

Clusters have been pre-randomized by number (by [name]), in blocks of 12, 12 and 16. The randomization plan was created on 25 July 2011 (http://www.randomization.com) using seed 11426, and stored securely. Project staff were not aware of the allocation during the process of consent for cluster inclusion.

### Blinding

Because of the nature of the intervention, allocation is not concealed.

### Data collection

Data are collected in baseline and endline censuses of cluster households. Two teams of six interviewers and one program officer cover a cluster at a time, defining its boundaries, mapping it and numbering the households. Each interviewer is allocated 10 households at a time, preferentially interviewing all married women aged 15 to 49 years. If none lives in a household, or if she is absent at three visits, another adult over 18 years of age is interviewed. The interview enumerates household members, their ages, schooling and livelihoods. It then covers duration of residence, assets and amenities, housing fabric, and faith. Women aged 15 to 49 years provide brief maternity histories and information on family planning. If they have been pregnant in the preceding 2 years, they are asked about antenatal care, delivery location and outcomes, and infant feeding. Information on immunizations and use of the ICDS is collected for all children under 5 years of age. Children are listed and their weights and heights are measured on designated days at the end of each cluster census. Data are entered on smartphones running Open Data Kit (ODK: http://opendatakit.org) on the Google Android operating system (http://www.android.com). A program officer will observe 5% of interviews. The interface includes generation of unique identifiers for women aged 15 to 49 years and children under 5 years of age, automatic skips and validation constraints to minimize error.

### Data management

Data are transferred electronically to a secure ODK Aggregate cloud repository on a password-protected Google Appspot. The dataset is downloaded twice weekly and run through automated error checks. Each week, 50 records (20 to 25% of interviews) are extracted after random numbering, printed on spreadsheets, and re-checked in the field. Data are also checked after download for errors in key fields, and monitoring summaries are produced through do-files written in Stata 12 (StataCorp, College Station, TX, USA; www.stata.com). The definitive dataset contains numerical identifiers for cluster, household number and participant. The names of heads of household and participants are collected during the interviews, but removed after storage. Access to data is restricted to the data manager and analysts. Datasets are backed up weekly on a server and compact discs.

### Interim analysis

A data monitoring committee (DMC) will meet three times (Figure 1) and follow the Data Monitoring Committees: Lessons, Ethics, Statistics guidelines [19]. At the first meeting, in May 2012, the committee considered the protocol, analysis plan, and baseline census from the 12 clusters in phase 1. Key questions were whether the baseline levels of outcome indicators accorded with our projections, and whether allocation was balanced. The second meeting will consider data from all three baseline phases and discuss any need for changes in the intervention approach, and the third will review the analysis plan against interim outcome data.

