### Trial design

The study is a cluster randomized controlled trial in which 20 slum areas will be allocated to have community resource centers and 20 will act as controls. Allocation will be done in three blocks, of 12, 12 and 16 clusters, in a phased design with 6-month intervals between the start of each phase (Figure 1). It has been our experience that, in large cluster randomized controlled trials, instituting interventions simultaneously in all clusters is problematic. The phased design is logistically feasible and, we hope, will allow clear demarcation of intervention start times. We will conduct two rounds of data collection: a baseline census and a census after 2 years of intervention, in which the information is provided mainly by married women aged 15 to 49 years.

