### Analysis plan

An analysis plan was discussed at the first meeting of the DMC in May 2012, and has been sealed. Presentation will follow the Consolidated Standards for the Reporting of Trials guidelines [20,21], beginning with a trial profile describing numbers of clusters, households, women and children enrolled in the evaluation, a summary of deviations from protocol, and a description of recruitment. Markers of identification will not be retained in analytical datasets. We will present a baseline comparison of allocation groups, summarizing household numbers, socioeconomic descriptors, including the Multidimensional Poverty Index [22], women’s age, education, and duration of residence, and numbers of births, and children under 2 and under 5 years of age. We will compare the primary outcomes between allocation arms, using data from the endline census after 2 years of intervention. Provided that distribution criteria are met, we will use logistic regression with a random effect for cluster [18], adjusted for phase (the second option being generalized estimating equations). We will enter each outcome as a dependent variable and allocation as a binary independent variable. If substantial baseline imbalances between allocation groups in demographic and socioeconomic characteristics are noted at the second DMC, we will include them as independent variables in multivariable models. If there are baseline imbalances in primary and secondary outcomes, we will model change in proportion between baseline and endline.

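### The third DMC meeting is to review a sealed analysis plan against interim outcome data, and nothing stated bars a change to the primary analysis on that basis

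*Protocol article*

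**What the plan says.** The protocol article treats the analysis plan as closed early. Under Analysis plan: "An analysis plan was discussed at the first meeting of the DMC in May 2012, and has been sealed". Under Interim analysis, the first DMC meeting is reported as the one at which "the committee considered the protocol, analysis plan, and baseline census from the 12 clusters in phase 1".

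The later meetings are described in one sentence. The second is confined to baseline data and the running of the intervention: "The second meeting will consider data from all three baseline phases and discuss any need for changes in the intervention approach". Outcomes appear only at the last of the three meetings, where the task given is that "the third will review the analysis plan against interim outcome data". The text does not say what the third review may decide, whether outcomes are shown by arm, or whether the sealed plan stands unchanged afterwards. Under Sample size the authors add that "we are not specifying stopping rules".

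Three parts of the primary analysis are conditional under Analysis plan:

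- **Model.** "Provided that distribution criteria are met, we will use logistic regression with a random effect for cluster", with GEE as the second option. The criteria are not given.
- **Covariates.** Demographic and socioeconomic variables enter if substantial imbalance is seen at the second DMC meeting.
- **Endline or change.** If outcomes are imbalanced at baseline, change from baseline is modelled instead of the endline proportion. No threshold and no decision date are given.

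On timing, Trial design says "We will conduct two rounds of data collection: a baseline census and a census after 2 years of intervention", with clusters entering in blocks of 12, 12 and 16 "in a phased design with 6-month intervals between the start of each phase".

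**The concern.** Sealing a plan is meant to keep the choice of analysis out of reach of the outcomes. The third meeting, as worded, brings the two together, and that is the only use the article states for the interim outcome data. No stopping rule is specified that the look would serve, and the sentence names no safety or data-quality task.

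This matters because the primary analysis still has unsettled parts. If one of them is settled, or merely confirmed, by someone who has seen how the arms differ, the test no longer has its nominal error rate. Choosing between two options that the sealed plan already contains would also leave no visible amendment, so a dated sealed copy would not reveal it. Readers could then not take the primary analysis as prespecified.

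**Working it through.** **1. Which data could be seen.** There are two censuses, baseline and after 2 years. Interim outcome data are therefore presumably endline records from phases that finish first: 12 clusters after phase 1, or 12 + 12 = 24 after phase 2, out of 40. Those records are also part of the primary analysis. The text does not date the third meeting; it points to Figure 1, which is not available here.

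**2. Which choices are exposed.**

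| Choice | Trigger stated | Decision time stated | Exposed at third meeting? |
|---|---|---|---|
| Random effects or GEE | Unspecified distribution criteria | None | Yes |
| Endline or change | Baseline imbalance in outcomes, no threshold | None | Yes |
| Covariates | Substantial baseline imbalance | Second DMC meeting (baseline data) | No |

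**3. Size, for endline or change.** The protocol gives no figure for this, so it is an illustration. Inputs from Table 1 are the control proportion p, records per cluster m, and between-cluster coefficient of variation k. Assumptions, not in the documents:

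- two-sided alpha of 0.05;
- stability s of true cluster proportions from baseline to endline, 0.4 to 1.0;
- the same m and variance at both censuses.

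Reliability of an observed cluster proportion is R = k²p² / [k²p² + p(1−p)/m]. The baseline–endline correlation is ρ = R × s. With equal variances, the endline and change statistics correlate at r = √[(1−ρ)/2].

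- Unmet need (p 0.46, m 350, k 0.11): R = 0.00256 / (0.00256 + 0.00071) = 0.783; ρ 0.313 to 0.783; r 0.586 to 0.329.
- Immunization (p 0.66, m 160, k 0.22): R = 0.02108 / (0.02108 + 0.00140) = 0.938; ρ 0.375 to 0.938; r 0.559 to 0.177.
- Wasting (p 0.20, m 150, k 0.10): R = 0.00040 / (0.00040 + 0.00107) = 0.273; ρ 0.109 to 0.273; r 0.667 to 0.603.

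Under no effect, the analysis with the larger interim |z| is chosen and then tested on all 40 clusters. The interim statistic correlates with its final counterpart at √t, where t = 12/40 = 0.3 or 24/40 = 0.6. If all 40 are seen, the error is P(either |z| > 1.96) from the bivariate normal.

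| Type I error, s = 0.4 to 1.0 | 12 seen | 24 seen | 40 seen |
|---|---|---|---|
| Unmet need | 6.7–7.0% | 7.9–8.5% | 8.8–9.5% |
| Immunization | 6.7–7.0% | 8.0–8.6% | 8.9–9.7% |
| Wasting | 6.5–6.6% | 7.7–7.9% | 8.5–8.7% |

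**4. Cross-check.** A separate simulation used 20 v 20 cluster summaries in blocks of 12, 12 and 16, adjusted for phase, with assumed baseline–endline correlation 0 to 0.9 and 8,000 runs per setting. Endline or change alone, fixed in advance, held 4.8–5.5%. Taking the smaller p-value of the two on full data gave 8.3–9.5%, in line with the last column.

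**The case against.** The strongest reply is that the article says review, not revise. The plan is called sealed, the DMC follows published guidelines, and the meeting may only check that the plan is workable, for instance that the distribution criteria hold. A DMC charter or the full plan, neither of which is shown, may forbid any change. This stands to a degree: a reader might infer that the investigators intend to alter the analysis once results are seen, and the documents do not say so. They also do not say that the DMC sees results by arm. What remains is that the published sentence sets the plan against outcome data and states no limit.

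A second reply is that the switch to change from baseline is triggered by baseline imbalance, which is knowable at the second meeting. That is correct, and it is why the fix is easy. But without a threshold or a date the decision can still be open at the third meeting.

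Two further inferences go too far. Covariate selection is not exposed, because it is tied to the second meeting, which sees baseline data. And an error rate near 9–10% is not what an interim look would produce; that needs all 40 clusters to be seen.

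Finally, the absence of stopping rules does not make an outcome look worthless. A DMC may have good reason to look for harm by arm.

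**Conclusion.** The point holds as an inconsistency in stated procedure: a sealed plan is to be reviewed against outcome data that would presumably also enter the primary analysis, while two primary-analysis choices lack a threshold and a decision date. It is not evidence of an intended change.

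The plausible worst case is a per-outcome type I error of 6.5–7.0% with phase 1 seen and 7.7–8.6% with phases 1 and 2 seen, against an assumed 5%. These figures rest on the assumed alpha, the assumed stability range, results being visible by arm, and a choice made purely by the larger test statistic. A more restrained review would inflate less. No figure is given for the choice between random effects and GEE. The change should be made, because it protects all three primary outcomes at almost no cost.

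**What to change.** Replace the clause on the third meeting under Interim analysis, and align Analysis plan with it, so that the text says:

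- the choice of model and the choice between endline and change are fixed at the second DMC meeting, from baseline data only, by stated criteria;
- the plan is then locked before the first endline record is collected;
- the third meeting may review data quality, coverage and harm, by arm and in confidence if the DMC needs it, but may not alter the primary analysis;
- any later change is reported as post hoc.

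Restricting the DMC to pooled outcomes is not needed once the plan is locked, and would hide harm by arm.

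The timetable allows this. Baseline collection began in September 2011 and runs 18 months, to about March 2013. Phase 1 centers opened in February 2012, so the first endline records fall about February 2014, leaving roughly 11 months. The cost is a short edit to the protocol and the matching line in the DMC's terms of reference, with no extra data or staff.

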### Analysis plan

An analysis plan was discussed at the first meeting of the DMC in May 2012, and has been sealed. Presentation will follow the Consolidated Standards for the Reporting of Trials guidelines [20,21], beginning with a trial profile describing numbers of clusters, households, women and children enrolled in the evaluation, a summary of deviations from protocol, and a description of recruitment. Markers of identification will not be retained in analytical datasets. We will present a baseline comparison of allocation groups, summarizing household numbers, socioeconomic descriptors, including the Multidimensional Poverty Index [22], women’s age, education, and duration of residence, and numbers of births, and children under 2 and under 5 years of age. We will compare the primary outcomes between allocation arms, using data from the endline census after 2 years of intervention. Provided that distribution criteria are met, we will use logistic regression with a random effect for cluster [18], adjusted for phase (the second option being generalized estimating equations). We will enter each outcome as a dependent variable and allocation as a binary independent variable. If substantial baseline imbalances between allocation groups in demographic and socioeconomic characteristics are noted at the second DMC, we will include them as independent variables in multivariable models. If there are baseline imbalances in primary and secondary outcomes, we will model change in proportion between baseline and endline.

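### Switching to change in proportion when baseline outcomes look imbalanced over-corrects a chance imbalance; adjusting every primary model for the baseline outcome avoids this and is more precise

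*Protocol article*

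**What the plan says.** All the relevant text is in the protocol article, mostly in the Analysis plan section.

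- Default data: "We will compare the primary outcomes between allocation arms, using data from the endline census after 2 years of intervention".
- Default model: "we will use logistic regression with a random effect for cluster [18], adjusted for phase", with allocation as the binary predictor. The baseline value of the outcome is not in the model.
- Outcome imbalance: "If there are baseline imbalances in primary and secondary outcomes, we will model change in proportion between baseline and endline". The text gives no size of imbalance and does not say whether the switch is made outcome by outcome.
- Covariates: "If substantial baseline imbalances between allocation groups in demographic and socioeconomic characteristics are noted at the second DMC, we will include them as independent variables".

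The Trial design section shows that baseline outcomes will be available in every cluster: "We will conduct two rounds of data collection: a baseline census and a census after 2 years of intervention".

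**The concern.** The observed baseline decides which estimator is used, and the one it selects suits the situation poorly. A difference between randomized arms at baseline is a chance difference, and only part of it is expected to persist to endline. Subtracting the whole of it over-corrects, and the rule does so only when there is an imbalance to over-correct. The arm that happened to start worse then appears to improve more.

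The baseline cluster proportions also carry sampling error, and subtraction adds that error to the outcome. If the switch does not fire, the baseline outcomes stay out of the model and the precision they offer is lost. The covariate rule has a related weakness: variables enter because they look imbalanced, not because they predict the outcome.

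At stake are the error rate and precision of the three primary comparisons. The effect scale may also be at stake, since change in proportion need not be reported as an odds ratio.

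**Working it through.** **Inputs.** From Table 1 (records per cluster m, coefficient of variation k, control and intervention proportions p0 and p1):
- unmet need: 350, 0.11, 0.46, 0.41
- incomplete immunization: 160, 0.22, 0.66, 0.53
- wasting: 150, 0.10, 0.20, 0.16

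There are 20 clusters per arm ("20 slum areas will be allocated to have community resource centers and 20 will act as controls"), and "The estimates were all made at 80% power". The following are not in the article and are assumed: a two-sided 5% level; the stability s of true cluster prevalences between censuses; a trigger at a baseline difference of more than 1 or 1.96 standard errors (SE); and largely independent sampling errors in the two censuses.

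**1. Reproducing Table 1.** Clusters per arm: c = 1 + (1.96+0.84)² × V/(p0-p1)², with V = p0(1-p0)/m + p1(1-p1)/m + k²(p0²+p1²).
- Unmet need: V = 0.000710 + 0.000691 + 0.004594 = 0.005995, so c = 1 + 7.85 × 0.005995/0.0025 = 19.8. Power with 20 clusters is 80%, so the row reproduces.
- Immunization: c = 18.5, power 83%. It agrees after rounding.
- Wasting: V = 0.001067 + 0.000896 + 0.000656 = 0.002619, so c is about 14. With 20 clusters the SE is √(0.002619/19) = 0.01174, 0.04/0.01174 = 3.41, and power is about 93%. The row is conservative.

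**2. Reliability of a cluster proportion.** R = k²p0²/[k²p0² + p0(1-p0)/m], and r = R × s.
- Unmet need: 0.00256/(0.00256+0.00071) = 0.78
- Immunization: 0.02108/(0.02108+0.00140) = 0.94
- Wasting: 0.00040/(0.00040+0.00107) = 0.27

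**3. Precision.** Relative to endline-only, the variance is 2(1-r) for change and 1-r² for baseline adjustment. Their ratio is 2/(1+r), which exceeds 1 whenever r<1, so change always loses to adjustment. Change loses to endline-only only if r<0.5. The break-even stability is 0.5/0.78 = 0.64 for unmet need and 0.5/0.94 = 0.53 for immunization. Wasting stays below 0.5 even at s = 1.

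Wasting, s = 1.0 to 0.8 (r = 0.27 to 0.22):
- Change: variance ratio 1.45 to 1.56; power from 3.41/√1.45 and 3.41/√1.56 is 81% to 78%.
- Adjustment: ratio 0.93 to 0.95; power about 94%.
- With the control-arm variance used in both arms, the figures are 90% endline-only, 76% to 73% change, and 92% to 91% adjusted.

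Unmet need and immunization at s = 0.6 (r = 0.47 and 0.56):
- Adjustment: ratio 0.78 and 0.68, a variance reduction of 22% and 32%. A nominal 80% power becomes 89% (2.80/√0.78 = 3.17) and 92% (2.80/√0.68 = 3.39).
- Change: ratio 1.06 and 0.87, close to endline-only. At s = 0.8 it is 0.75 and 0.50, better than endline-only.

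**4. Error given a baseline difference d.** Under no effect, change is off by -(1-r)d, endline-only by +rd, and adjustment by about 0.
- Wasting: the SE of the baseline difference is √(2 × 0.001467/20) = 1.2 points. A 2-SE imbalance is 2.4 points, and change is off by 1.8 to 2.1 points (r = 0.27 to 0.14) against a 4-point target.
- Unmet need: a 2-SE imbalance is 3.6 points. At r = 0.39, change is off by 2.2 points and endline-only by 1.4 the other way, against a 5-point target.

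**5. Type I error.** Simulated null trials (40,000 per setting, 20 v 20 clusters, cluster-level t-tests without phase). The three middle columns are conditional on the trigger being met; the last is over all trials.

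| r | Trigger (SE) | Change | Endline-only | Adjusted | Whole rule |
|---|---|---|---|---|---|
| 0.14 | 1 | 11.7% | 5.5% | 4.8% | 7.0% |
| 0.14 | 1.96 | 28.6% | 5.3% | 3.7% | 6.0% |
| 0.27 | 1 | 10.1% | 6.2% | 4.7% | 6.3% |
| 0.27 | 1.96 | 23.2% | 7.0% | 4.1% | 5.5% |
| 0.70 | 1 | 7.4% | 12.6% | 4.9% | 3.4% |
| 0.70 | 1.96 | 11.8% | 31.4% | 5.0% | 3.9% |
| 0.90 | 1 | 5.9% | 15.2% | 4.8% | 2.0% |
| 0.90 | 1.96 | 6.9% | 55.9% | 4.9% | 2.4% |

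A normal approximation gives about 11% to 12% (1 SE) and 25% to 29% (1.96 SE) for change at r = 0.27 to 0.14. The trigger is met for a given outcome in about 32% and 5% of trials respectively. Mean bias of the whole rule over all trials is zero to simulation error.

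**The case against.** Much can be said for the plan, and most of it stands.

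- The default endline comparison is valid, and the trigger uses baseline data only. This is not selection on endline results.
- A reader might infer that the primary result is biased outright. It is not: the error is conditional on an observed imbalance and cancels over randomizations. Endline-only is conditionally off as well, and by more than change when r exceeds 0.5. For stable outcomes the switch therefore improves on the plan's own default.
- A reader might infer that change is always less precise than endline-only. Step 3 shows that this depends on r, and the article gives no stability figure for any outcome.
- A reader might apply the wasting variance ratios to the nominal 80% and conclude that power falls to between 61% and 64%. Table 1's wasting row starts near 93%, so the loss ends near the planned level.
- A reader might say that the baseline census goes unused unless the switch fires. The article uses it for the baseline comparison, the sample size inputs, the data monitoring committee's review and conditional covariates. Only the baseline outcomes are left out of the model.
- The 0.27 for wasting is a ceiling only if sampling errors are independent. The same clusters are visited twice, and some children will be measured both times, which could raise r.
- The sealed analysis plan is not shown and may define the trigger. But no threshold removes the over-correction or makes change as precise as adjustment, so the point does not depend on it.

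**Conclusion.** The concern holds in a limited form. Once an imbalance triggers the switch, change over-corrects by (1-r)d and is less precise than adjusting for the baseline outcome at every r below 1.

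The cost is clearest for wasting. Power is about 78% to 81% with change, against 93% endline-only and 94% with adjustment (stability 0.8 to 1.0). Conditional type I error is about 11% or 25% to 29% (23% to 29% in simulation), depending on the assumed trigger, against 5% with adjustment.

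Over all randomizations the two-stage rule has a type I error of about 6% to 7% at the wasting correlations and 2% to 4% for r of 0.7 to 0.9. It is therefore not held at 5% in either direction, but the departure is modest. For unmet need and immunization, the likelier loss is in the branch without a switch, which forgoes a variance reduction of about 22% and 32% at an assumed stability of 0.6.

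The documents do not support calling the trial's primary result biased overall, or change less precise than endline-only for all three outcomes. The figures rest on the assumed two-sided 5% level, the stability range, the two triggers, and largely independent sampling errors between censuses.

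**What to change.** Before endline data are seen, delete the imbalance-triggered switch to change. For each primary outcome, fit the endline random-effects logistic model adjusted for phase and for that outcome's baseline cluster-level proportion, whatever balance is observed. Use the proportion itself, or a continuity-corrected log-odds where a cluster is at 0% or 100%.

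Do the same for secondary outcomes with adequate baseline numbers per cluster. With about 80 children under 2 per cluster, the feeding indicators at 6 to 8 months (80 × 3/24 = 10 children) and 12 to 15 months (80 × 4/24, about 13) are probably too sparse.

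Name any demographic or socioeconomic covariates in advance, by expected prognostic value. This replaces the rule that begins "If substantial baseline imbalances between allocation groups in demographic and socioeconomic characteristics are noted at the second DMC".

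The cost is one cluster-level degree of freedom out of 40 clusters and a documented amendment to the sealed analysis plan. No new data are needed. For wasting the gain over endline-only is small, 1 to 2 points of power; the benefit there lies in not switching to change.
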